### 2.2.2 Secondary endpoint

As secondary outcomes we will collect:

- symptomatic, objectively confirmed fatal and non-fatal HA-VTE during hospitalization
- all-cause mortality during hospitalization and up to 90 days after admission
- major bleeding during hospitalization and up to 90 days after admission. Major bleeding will be defined as fatal bleeding, symptomatic bleeding at critical sites (intracranial, intraspinal, intraocular, retroperitoneal, intraarticular, pericardial, or intramuscular with compartment syndrome), or bleeding with a reduction of hemoglobin of at least 20 g/L or bleeding leading to transfusion of 2 or more units of packed red blood cells according to the definition of the International Society on Thrombosis and Haemostasis.
- clinically relevant non-major bleeding during hospitalization and up to 90 days after admission. Clinically relevant non-major bleeding will be defined as overt bleeding that does not meet criteria for major bleeding but is associated with a medical intervention, unscheduled physician contact (visit or telephone call), or pain or impairment of activities of daily life
- Patient autonomy in the activities of daily living at discharge and at 90 days after admission using the modified Barthel Index
- Length of hospital stay, defined as the time/date of discharge minus time/date of admission at the hospital ward.
- Subsequent hospitalization (readmission) up to 90 days after admission.

### 2.2.3 Assessment of endpoints

To obtain information on the occurrence and timing of outcome events, study personnel will conduct patient visits on the day prior or the day of discharge, and will contact patients, family members, and/or primary care physicians by phone at 90 days after admission.

Medical records will be collected and reviewed to obtain information about the date/type/circumstances of medical outcome events (HA-VTE, major and clinically relevant non-major bleeding, death). In patients who experienced HA-VTE, radiographic reports and images will be obtained. For patients who died, the cause of death based on medical reports, death certificates, and autopsy reports (if available) will be recorded.

Patient's autonomy in the activities of daily living will be assessed using the modified Barthel index in a face-to-face interview at hospital discharge, and by phone at 90 days after admission. The modified Barthel Index has been reported as being the most accurate scale to assess activities of daily living (ADL) and has thus been widely used as a measure of autonomy. The modified version improves the internal consistency and provides a better discrimination of functional ability compared to the original version. The patient's ability to perform different ADLs will be rated as follows: fully independent, with minimal or moderate help, attempts task but unsafe, and unable to perform. The maximum point score is 100; a total modified Barthel Index point score of 0-20 suggests total, 21-60 severe, 61-90 moderate, and 91-99 slight dependence. A point score of 100 indicates that the patient is independent of assistance from others.

To assess length of hospital stay, admission and discharge times/dates will be obtained from hospital charts. The number of subsequent hospitalizations up to 90 days after admission will be obtained through patient interview during the follow-up phone call, interview of the patient's primary care physician, or hospital chart review.

All medical outcome events (HA-VTE, major and clinically relevant non-major bleeding, and death) will be adjudicated by a committee of 3 independent clinical experts. Based on available information, death will be adjudicated as PE-related, due to another cause, or due to an undetermined cause (if the cause of death is undetermined based upon the clinical information, or if no or insufficient information is available to determine the cause of death). Death will be considered PE-related in the following situations: a) autopsy-confirmed PE in the absence of another more likely cause of death, or b) objectively confirmed PE within the last 48 hours before death in the absence of another more likely cause of death, or c) PE is not objectively confirmed, but is most likely the main cause of death (personal communication from the International Society of Thrombosis and Haemostasis working group for the Classification of the Cause of Death in VTE Studies). For death due to a cause other than PE, the cause will be recorded using the World Health Organization definitions (bleeding, acute coronary syndrome, ischemic stroke, left ventricular failure, sudden death without known etiology, cancer, and other). The final adjudication will be based on the committee's consensus.

## 2.3 Project design

We will conduct a multicenter national non-interventional prospective cohort study including consecutive consenting adult patients admitted to general internal medicine at ≥3 large-volume Swiss hospitals. VTE risk will be assessed at admission using the simplified Geneva score, and 3 other validated RAMs. Mobility will be measured during the hospitalization using accelerometry. Patients will be followed for the occurrence of HA-VTE, with a follow-up phone call at 3 months after admission (**Figure 3**).

**Figure 3. Prospective cohort study on risk stratification for hospital-acquired VTE in hospitalized medical patients**

[figure not shown]

### 3 PROJECT POPULATION AND STUDY PROCEDURES

#### 3.1 Project population, inclusion and exclusion criteria

Overall, 1350 consecutive adult patients hospitalized for acute illness in general internal medicine will be invited to participate in this study upon admission if they meet the following eligibility criteria:

- **Inclusion criteria:**
  - 1) age  $\geq 18$  years
  - 2) admitted for hospitalization  $>24$  hours on a general internal medicine ward
  - 3) informed consent as documented by signature
- **Exclusion criteria:**
  - 1) need for therapeutic anticoagulation (e.g., atrial fibrillation)
  - 2) life expectancy  $<30$  days
  - 3) insufficient proficiency of the German or French language
  - 4) unwilling to provide informed consent
  - 5) prior enrolment in the study

For participants who are unable to give informed consent due to mental illness or cognitive impairment, permission to participate in the study will be obtained from a legally authorized representative. We will not exclude these patients, because the risk of VTE and immobilization and the associated adverse outcomes are particularly high in the elderly, where cognitive impairment is more prevalent.

#### 3.2 Recruitment, screening and informed consent procedure

Consecutive hospitalized medical patients will be screened for recruitment at the General Internal Medicine wards of at 3 large Swiss hospitals. Study nurses will screen newly admitted patients ( $n \approx 12-15$  per hospital/day) on a daily basis for eligibility. Reasons for exclusion will be recorded for all patients. Potentially eligible patients will receive the participant information sheet. The investigators or delegated study members will explain to each participant the nature of the study, its purpose, the procedures involved, the expected duration, the potential risks and

benefits and any discomfort it may entail. Potential participants will be informed that the participation in the study is voluntary and that they may withdraw from the study at any time and that withdrawal of consent will not affect subsequent medical assistance and treatment. They will be informed that their medical records may be examined by authorised individuals other than their treating physician. The potential study participants will have time to read the participant information, and they will have the opportunity to ask questions. Ample time (up to 24 hours) will be given to study candidates to consider their participation. The investigator or his/her delegate will ask eligible patients who are interested in study participation to provide informed consent and sign and date the approved consent form. The consent form will also be signed and dated by the investigator or delegated study team member after the participant has signed, and it will be retained as part of the study records. A copy of the signed document will be given to the study participants.

Screening of patients who are admitted on weekends or holidays will occur on the next working day. To assess generalizability of enrolment, demographic data (age, year of birth, sex) without any identifying, patient-specific information and the reasons for exclusion will be recorded for all patients who fulfill one or more exclusion criteria or who do not consent to participate.

No payment or compensation will be given to study participants.

Given that >9'000 patients are hospitalized at the general internal medicine wards of two of the participating hospitals annually, and assuming that 70% of the patients will be eligible and >50% will agree to participate based on pilot data and previous experience, achieving the target sample size of 1350 over a recruitment period of 15 months is highly feasible. Patient enrolment will be continuously monitored to ensure that recruitment goals are met.

If the observed enrolment rates should be unexpectedly lower than anticipated, we will reassess the recruitment plan and alter the recruitment strategy, e.g. by considering additional study sites or by extension of the recruitment phase to achieve the target sample size.

### 3.3 Study procedures

#### 3.3.1 Planned project timeline

The overall duration of the study phase of this project is planned to be 18 months (we plan a 15 months recruitment period, and 3 months follow-up period; see **Table 2**). Each patient will be followed for 3 months after inclusion.

**Table 2. Planned Project Timeline**

| Tasks                                  | Project Month | 5 | 6 | 7 | 8 | 9 | 10 | 11 | 12 | 1 | 2 | 3 | 4 | 5 | 6 | 7 | 8 | 9 | 10 | 11 | 12 | 1 |
|----------------------------------------|---------------|---|---|---|---|---|----|----|----|---|---|---|---|---|---|---|---|---|----|----|----|---|
| STUDY PHASE (18 months)         |               |   |   |   |   |   |    |    |    |   |   |   |   |   |   |   |   |   |    |    |    |   |
| Patient recruitment                    |               |   |   |   |   |   |    |    |    |   |   |   |   |   |   |   |   |   |    |    |    |   |
| Patient follow-up                      |               |   |   |   |   |   |    |    |    |   |   |   |   |   |   |   |   |   |    |    |    |   |
| CLOSE OUT (3 months)            |               |   |   |   |   |   |    |    |    |   |   |   |   |   |   |   |   |   |    |    |    |   |
| Data cleaning                          |               |   |   |   |   |   |    |    |    |   |   |   |   |   |   |   |   |   |    |    |    |   |
| Data analysis                          |               |   |   |   |   |   |    |    |    |   |   |   |   |   |   |   |   |   |    |    |    |   |
| Preparation of reports and manuscripts |               |   |   |   |   |   |    |    |    |   |   |   |   |   |   |   |   |   |    |    |    |   |
| Dissemination of results               |               |   |   |   |   |   |    |    |    |   |   |   |   |   |   |   |   |   |    |    |    |   |

### 3.3.2 Patient timeline

**Table 3. Timeline of patient enrolment and schedule of assessments**

| Study Period                                         | Screening                       | Enrolment & Baseline |                     | Follow-up                           | Close-out        |
|------------------------------------------------------|---------------------------------|----------------------|---------------------|-------------------------------------|------------------|
| Visit / Follow-up phone call                         | Screening                       | 1                    |                     | 2                                   | 3 ①   |
| Time (day with allowed visit window)                 | d ≤ -1                          | d0                   | d1 (1-3)            | dx                                  | d90 (85-95)      |
| Description of time point                            | Hospital admission  |                      | Day after inclusion | Day prior to discharge  | End of follow-up |
| Eligibility screen                                   | x                               |                      |                     |                                     |                  |
| Oral and written information                         | x                               |                      |                     |                                     |                  |
| Written informed consent                             |                                 | x                    |                     |                                     |                  |
| Baseline characteristics                      |                                 |                      |                     |                                     |                  |
| Contact information                                  |                                 | x                    |                     |                                     |                  |
| Demographic characteristics                          |                                 | x                    |                     |                                     |                  |
| Items of the RAMs                                    |                                 | x                    |                     |                                     |                  |
| Comorbidities                                        |                                 | x                    |                     |                                     |                  |
| Contraindications to pharmacological VTE prophylaxis |                                 | x                    |                     |                                     |                  |
| Laboratory findings                                  |                                 | x                    |                     |                                     |                  |
| Medications at admission                             |                                 | x                    |                     |                                     |                  |
| Treatments since admission                           |                                 | x                    |                     | x                                   | x                |
| Autonomy: modified Barthel Index                     |                                 | x                    |                     | x                                   | x                |
| Pressure sore risk: Braden scale                     |                                 | x                    |                     |                                     |                  |
| Mobility measurements                         |                                 |                      |                     |                                     |                  |
| Distribution of accelerometer & instructions         |                                 | x                    |                     |                                     |                  |
| Accelerometry                                        |                                 |                      |                     |                                     |                  |
| Physician's estimation of physical activity level    |                                 |                      | x                   |                                     |                  |
| Ability to walk                                      |                                 | x                    |                     |                                     |                  |
| Feasibility Substudy              |                                 |                      |                     |                                     |                  |
| Consent for hypothetical RCT                         |                                 |                      |                     | x                                   |                  |
| Medical Outcomes                              |                                 |                      |                     |                                     |                  |
| Symptomatic HA-VTE                                   |                                 |                      |                     | x                                   | x                |
| All-cause mortality                                  |                                 |                      |                     | x                                   | x                |
| Major bleeding                                       |                                 |                      |                     | x                                   | x                |
| Clinically relevant non-major bleeding               |                                 |                      |                     | x                                   | x                |
| Other study data                              |                                 |                      |                     |                                     |                  |
| Length of hospital stay                              |                                 |                      |                     | x                                   |                  |
| Discharge location                                   |                                 |                      |                     | x                                   |                  |
| Duration of VTE prophylaxis                          |                                 |                      |                     | x                                   |                  |
| Subsequent hospitalizations                          |                                 |                      |                     |                                     | x                |

 Enrolment and baseline visit may take place within 72 hours of admission

 The final visit during the hospital stay will take place the day prior to discharge or on the day of discharge.

 Recruitment feasibility for a future hypothetical randomized controlled trial (RCT) will be assessed in patients from one study site (Inselspital) who meet potential eligibility criteria for this hypothetical trial.

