## 2.2 Primary and secondary endpoints

### 2.2.1 Primary endpoint

The primary outcome will be symptomatic, objectively confirmed fatal and non-fatal HA-VTE, including symptomatic distal and proximal DVT and PE up to 90 days after hospital admission.

The objective diagnostic criteria for a PE diagnosis will be based on available radiographic or autopsy reports, and will include a new intraluminal filling defect on computed tomography pulmonary angiography (CTPA) or pulmonary angiography; a perfusion defect involving at least 75% of a segment, with corresponding normal ventilation (i.e., high probability lung scan); the confirmation of a new PE on autopsy, or an objectively confirmed proximal DVT with clinical signs and symptoms of PE. The objective diagnosis of DVT will be the non-compressibility of a venous segment on compression ultrasonography or an intraluminal filling defect on contrast venography. Because iliac veins and the inferior vena cava may be technically difficult to compress, additional diagnostic criteria for iliac and caval DVT will also include abnormal duplex flow patterns compatible with thrombosis or an intraluminal filling defect on spiral computed tomography or magnetic resonance imaging venography. We will consider both proximal and distal symptomatic DVTs. In line with previous studies on VTE prophylaxis and given similarities in some risk factors and outcomes, symptomatic upper extremity DVT will also be considered as a study outcome, although its incidence is expected to be low. VTE events diagnosed during the first 48 hours of hospitalization will not be considered as a primary outcome for this study in order to rule out pre-existing VTE that occurred prior to hospital admission.

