#### **4.1.2 Statistical analyses**

Work package 1) Time to event analyses with competing risk methods will be used to assess the prognostic performance of the simplified Geneva score and the other RAMs (**Table 1**) and their association with HA-VTE, with non-VTE death representing the competing risk. We will use a subdistribution hazard model of Fine and Gray to assess the association of the simplified Geneva score and the other RAMs with VTE, calculating subhazard ratios with 95% CIs. These analyses will be adjusted for the use of TPX and study site. Cumulative incidences of HA-VTE in low- and high-risk score patients will be assessed and graphically presented to assess calibration and compare different RAMs. The time-dependent area under the curve (AUC) as well as sensitivity, specificity, and positive and negative predictive values will be calculated for each RAM to assess their accuracy to predict HA-VTE at 90 days using time-dependent receiver operating characteristic (ROC)-curve analysis, taking into account censored data and competing events. Additionally, because some patients will be treated with TPX and thus have a lower risk of VTE, we will perform separate sensitivity analyses in patients with and without TPX. It is possible that a small number of patients will be started on therapeutic dose anticoagulation for reasons other than VTE (e.g. new onset atrial fibrillation) during follow-up; these patients will be censored in the main analysis.

Secondary time-to-event outcomes (major and clinically relevant non-major bleedings) will also be evaluated using competing risk regression. For all-cause mortality, we will use an ordinary Cox regression, for length of stay an accelerated failure time model. Binary outcomes (in-hospital VTE and readmission) will be evaluated using logistic regression. The Barthel-index will be assessed using linear regression. All models will be adjusted for the use of TPX and study site.

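### Length of stay is counted from admission, but patients may enrol up to 72 hours later, so stays ending before enrolment are missed and the length-of-stay effect is modestly understated

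*Protocol*

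**What the plan says.** Section 2.2.2 lists length of stay as a secondary outcome, "defined as the time/date of discharge minus time/date of admission at the hospital ward". Section 4.1.2 plans "for length of stay an accelerated failure time model", adjusted for thromboprophylaxis and site. Substudy II (3.3.3.4) uses length of stay again, as an outcome of accelerometer-measured and nurse-rated mobility.

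Entry to the cohort can come later than admission. Table 3, footnote 1: "Enrolment and baseline visit may take place within 72 hours of admission". Section 3.2 makes some delay routine: "Screening of patients who are admitted on weekends or holidays will occur on the next working day", and "Ample time (up to 24 hours) will be given to study candidates to consider their participation". Inclusion criterion 2 in section 3.1 separately limits the cohort to hospitalizations of more than 24 hours.

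Neither 4.1.2 nor 4.2 mentions an entry time, left truncation or a landmark; 4.2 mentions only censoring for dropouts and deaths.

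For the other outcomes the origin is mixed. Section 2.2.1 counts "symptomatic distal and proximal DVT and PE up to 90 days after hospital admission", and 2.2.2 counts death and bleeding to 90 days after admission. Section 3.3.1 follows each patient for 3 months after inclusion, Table 3 puts day 0 at enrolment, 3.3.5 times the final call from inclusion, and 6.1 and 6.2 recode dates as days since enrolment.

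**The concern.** A patient who goes home at hour 40 and would have been approached at hour 45 is eligible by length of hospitalization but cannot be in the data. Whoever is enrolled at hour 45 has, by selection, a stay of at least 45 hours. An AFT model run from admission without an entry time treats those first 45 hours as time in which discharge could have been observed.

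The loss differs between groups. Whichever group has the shorter stays, for example low-risk or more mobile patients, loses more of its short stays, so the contrast shrinks. What is at stake is the length-of-stay secondary outcome, the Substudy II prognostic analyses, and the use of this cohort to relate mobility to length of stay, which section 1.2 foresees.

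**Working it through.** **No plan figure to reproduce.** The protocol gives no expected length of stay, no effect on it and no enrolment delay. The sample size of 1308 concerns HA-VTE and is not affected.

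**Inputs**
- From the protocol: entry up to 72 h after admission; weekend admissions screened on the next working day; up to 24 h to decide; stays over 24 h only; 67% high risk and 33% low risk (4.1.1).
- Assumed: lognormal stays with log-SD 0.75; low-risk median 4, 6 or 8 days; true high-to-low time ratio 1.30; screening at 09:00 on working days; consent after 0-6 h or 0-24 h. The clock time is an assumption; the protocol says only that screening is daily.

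**Mechanism, by hand.** The probability that a stay ends before day t is Φ((ln t − ln m)/0.75), where m is the median. Take enrolment at hour 48 and ask which eligible stays have ended between 24 and 48 h.
- Low risk, m = 4: Φ(−0.924) − Φ(−1.848) = 0.178 − 0.032 = 0.145. Among stays over 24 h: 0.145/0.968 = 15%.
- High risk, m = 4 × 1.30 = 5.2: Φ(−1.274) − Φ(−2.198) = 0.101 − 0.014 = 0.087. Among stays over 24 h: 0.087/0.986 = 9%.

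The group with shorter stays loses more, so the ratio falls.

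**Simulation.** The screening rule gives a mean admission-to-enrolment lag of 23-31 h, with 12-15% of participants entering after hour 48. The right comparison is with eligible patients (stay over 24 h), because dropping shorter stays is a choice of target population.

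| Low-risk median | Time ratio, eligible | Time ratio, enrolled | Low-risk median overstated by |
|---|---|---|---|
| 4 days | 1.26 | 1.24-1.25 | 4-6% |
| 6 days | 1.29 | 1.27 | 2-3% |
| 8 days | 1.295 | 1.28-1.29 | about 1% |

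Late enrolment alone loses about 1-5% of eligible patients. A left-truncated likelihood returns 1.29-1.32, that is, the 1.30 of the underlying lognormal.

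**Longer delays.** With enrolment uniform over 24-72 h, a true ratio of 1.50, median 4 days and log-SD 0.8, the ratio is 1.44 among stays over 24 h and 1.33 among those enrolled. With median 8 days and log-SD 0.6 it goes only from 1.50 to 1.48. The mean delay here is 48 h, well above what working-day screening produces, so this is a pessimistic bound.

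**HA-VTE.** Expected events: 1308 × (0.67 × 0.028 + 0.33 × 0.006) = 1308 × 0.02074 = 27.1. Section 2.2.1 says "VTE events diagnosed during the first 48 hours of hospitalization will not be considered as a primary outcome for this study", so only hours 48-72 are exposed. That day holds 27.1 × 1/88 = 0.3 events if the hazard is flat over days 2-90, and 0.9 to 2.6 if it is front-loaded (exponential, mean 30 to 10 days). With at most 15% entering after hour 48, even the highest figure means about 2.6 × 0.15 = 0.4 events missed.

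**Mortality.** Cox hazard ratios without and with an entry time are 1.996 and 1.997 in one simulated scenario, and 4.797 and 4.796 in another. Early deaths, 0.1-2.8% of patients in the scenarios tried, drop out of absolute risks.

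**The case against.** Four points can be made against this.

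- **The models' time origin is not stated.** This is right for Fine-Gray and Cox. Section 4.1.2 gives none, and several sections point to inclusion. It does not help for length of stay, whose start at admission is written into the endpoint definition.
- **Part of the apparent attenuation comes from eligibility.** This stands. At a 4-day median the ratio is already 1.26, not 1.30, once stays of 24 h or less are left out as section 3.1 requires. Against all admissions the enrolled ratio falls by up to 0.06; late enrolment explains only about 0.01-0.03 of that. The table above counts only this second part.
- **An entry time is analysis-plan detail.** A separate plan could add it, and nothing in 4.1.2 forbids it. But section 4.1 is itself titled as the statistical analysis plan, and the protocol fixes both the origin and the model for length of stay. Followed as written, the bias occurs.
- **The remedy is not free of assumptions.** This stands. A delayed-entry AFT model relies on its parametric form for the early part that nobody observes, which is why it returns about 1.30 rather than the 1.26 seen among eligible patients with a 4-day median. It also assumes that, given the covariates, enrolment timing is unrelated to how long the patient stays.

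**Conclusion.** The point holds for length of stay. The protocol measures it from admission, admits patients up to 72 hours later, and plans an AFT model without an entry time. Short stays are under-sampled, time ratios move towards 1 and the median is overstated. Under the stated assumptions the size is modest: about 1-5% of eligible patients lost, about 0.01-0.03 off a time ratio of 1.30, and about 1-6% on the low-risk median. These figures depend on stay and delay distributions that the protocol does not give; the direction does not vary across the scenarios tried.

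A reader might infer that the primary validation or the mortality results are biased too. The documents do not support that. The 48-hour rule leaves one day exposed for HA-VTE, worth well under one event at the expected delays; mortality hazard ratios are practically unchanged; and no origin for the Fine-Gray and Cox models is fixed. What remains for those outcomes is an ambiguity between admission and inclusion that should be settled. This is an inexpensive improvement to a secondary analysis, not a threat to the primary objective.

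**What to change.** In section 4.1.2, fit the length-of-stay AFT model with admission as time zero and each patient entering at the later of enrolment and 24 hours. Do the same for the Substudy II length-of-stay analyses. Alternatively, analyse remaining stay from enrolment, which avoids extrapolating into the unobserved early hours but answers a slightly different question. Report the distribution of the admission-to-enrolment delay.

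For HA-VTE, bleeding and death, state one time origin and reconcile sections 2.2.1 to 2.2.3 with 3.3.1, Table 3 and 3.3.5. If admission is kept, use the enrolment entry time there as well, including in the cumulative incidence and time-dependent ROC analyses so that all share one risk set. Little numerical change is expected.

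Cost: wording and slightly more complex code. Table 4 already collects admission and inclusion dates; recording the inclusion time would sharpen an entry measured in hours. When dates are recoded as days since enrolment, the admission day must be kept. The sample size does not change and patients carry no added burden.
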